### Secondary objective

To monitor changes in expression of leucocyte surface markers (primary outcome measures) over the time course of the ADAPT-Sepsis biomarker-guided antibiotic duration intervention period.

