### Definition of sepsis-associated immunosuppression

We will define ‘sepsis-associated immunosuppression’ as two or more abnormalities (from low HLA-DR, low CD88, raised PD-1 or raised percentage regulatory T cells) that persist for 3 or more days.^14 26^ Previous reports have shown that the persistence of immune dysfunctions is associated with worse clinical outcome, including increased hospital-acquired infections and death.^10 13 15^ The ‘non-immunosuppressed’ group will be patients who do not meet these criteria.

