### Data analysis plan

A formal analysis plan will be finalised and deposited on an open access platform before the database is locked.

For the primary objective, the time it takes for antibiotics to be stopped in patients during the ADAPT-sepsis biomarker-guided antibiotic phase will be summarised and the distribution of the outcome described for the ‘sepsis-associated immunosuppression’ and the ‘non-immunosuppressed’ groups. The mean number of antibiotic days will be compared between groups obtained from linear regression models and adjusted for confounding variables. In addition, each of the cellular markers will be assessed as a continuous outcome. The change in cellular markers between each time point will be correlated with the number of days on antibiotics using Spearman’s correlation coefficient. One sample t tests will be used to assess the changes between time points.

The trial outcomes of 28-day antibiotics, hospital-acquired infections and length of ICU-stay and hospital-stay will be summarised for the ‘sepsis-associated immunosuppressed’ and ‘non-immunosuppressed’ groups. Differences between groups will be assessed using linear regression for continuous variables and logistic regression for categorical variables. We will describe the difference between the groups using p values, point estimates and 95% CIs.

For the secondary objective, we will assess the difference in the PCT/CRP levels and cellular markers for patients who met the criteria for ‘sepsis-associated immunosuppressed’ and when immune profile recovered (ie, became ‘non-immunosuppressed’). Assessments will be captured over time, and we will compute a longitudinal analysis (taking time as a random effect) to assess the difference in the two groups.

Subgroup analyses:

Exploratory analysis will be carried out for the following subgroups:

Patients receiving critical care for a medical versus a surgical cause of sepsis;Patients receiving critical care because of trauma versus non-trauma;Patients receiving critical care because of a community-acquired infection versus a hospital-acquired infection;Infection site: community-acquired pneumonia; hospital-acquired pneumonia; urinary tract infection; intra-abdominal infection or positive blood culture;Patients with septic shock, as defined by persistent hypotension requiring vasopressors to maintain an mean arterial pressure (MAP) ≥65 mm Hg and a serum lactate of >2 mmol/L.^1^

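### The secondary-objective comparison of the phenotype's own defining markers between suppressed and recovered states is largely circular

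*Protocol article*

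**What the plan says.** All places are in the Protocol article.

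- **Definition of sepsis-associated immunosuppression.** The label requires "two or more abnormalities (from low HLA-DR, low CD88, raised PD-1 or raised percentage regulatory T cells) that persist for 3 or more days". The comparison "group will be patients who do not meet these criteria", so it is the complement.
- **Secondary objective.** The stated aim is "To monitor changes in expression of leucocyte surface markers (primary outcome measures) over the time course" of the intervention period. It does not depend on the label.
- **Data analysis plan, secondary-objective paragraph.** "we will assess the difference in the PCT/CRP levels and cellular markers for patients who met the criteria for" the immunosuppressed label "and when immune profile recovered (ie, became" non-immunosuppressed. The method follows: "we will compute a longitudinal analysis (taking time as a random effect) to assess the difference in the two groups".
- **Outcomes.** The marker families that define the label are also the declared primary outcome measures. PCT and CRP are secondary measures and are not part of the label.
- **Sampling and data collection.** Blood is taken on days 1, 3, 5 and 7.

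**The concern.** In the secondary-objective paragraph, the variables that sort patients or visits are also the response. A patient enters the suppressed state because at least two of the four markers are abnormal. The patient leaves it because fewer than two are abnormal. To find that those markers are worse in the first state than in the second largely restates the rule.

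The state contrast adds regression to the mean. Visits are selected for extreme values and then for less extreme ones, so part of any apparent improvement arises from visit-to-visit variation alone.

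The Rationale hopes that, if PCT and CRP come down while the cellular abnormalities clear, clinicians may trust biomarker-guided durations more. A recovery produced partly by the sorting rule would feed that inference. The contrast also does not answer the stated secondary objective, which concerns change over time and does not require patients to have met and then lost the label.

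**Working it through.** **Number analysed.** The plan's sample size was reproduced only to set the number of patients.

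- Per group: 2 × (1.960 + 1.282)² × 6² / 3² = 84.1, rounded up to 85, so 170 in total.
- With 5% withdrawal: 170 / 0.95 = 178.9, or 179 against the stated 180.
- Evaluable patients: 180 × 0.95 = 171. No sample-size figure is in dispute.

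**Hand illustration of regression to the mean.** Take a stable, standard normal marker, scored so that high is abnormal, with 30% of values abnormal (cut-off 0.524).

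- Mean of the abnormal values: density at the cut-off / 0.30 = 0.348 / 0.30 = 1.16 SD.
- If values at adjacent visits correlate at r, the expected next value is r × 1.16.
- r = 0.5: 0.58, an apparent improvement of 0.58 SD. r = 0.8: 0.93, an apparent improvement of 0.23 SD.
- The true change is zero. Selecting the later visit for no longer being abnormal widens the gap.

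**Simulations.** From the article: 171 patients, four markers, four visits, and the rule of two or more abnormalities that persist, read as the same markers being abnormal at two consecutive samples. Assumed, because the article gives none of them: cut-offs, correlations and the absence of any time trend. Both simulations use one population with no distinct subgroups.

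- *Simulation A* (300 studies per setting): independent markers, 30% or 50% of values abnormal, within-patient correlation 0.3 to 0.85. Recovered means a later visit with fewer than two abnormalities.
- *Simulation B* (1,000 studies per setting): 30%, 40% or 50% abnormal, adjacent-visit correlation 0.5 or 0.8, between-marker correlation 0 or 0.3. Within labelled patients, visits with two or more abnormalities are compared with visits with fewer than two. A variable unrelated to the markers is the negative control.

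| Quantity | A | B |
|---|---|---|
| Share of patients labelled | 19–67% | 25–70% |
| Defining marker, between groups, p<0.05 | 88–99% | 95–100% |
| All four markers p<0.05 in one study | not run | 80–100% |
| Group difference per marker | 0.42–0.65 SD | about 0.6–1.0 SD of patient means |
| Suppressed versus recovered, p<0.05 | 35–92% | 85–100% |
| Apparent change between states (true change zero) | 0.22–0.63 SD | not reported |
| Unrelated variable, between groups, p<0.05 | not run | 3.8–6.4% |
| Unrelated variable, between states, p<0.05 | not run | 3.5–6.0% |

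The negative control stays near the nominal 5%, so the excess comes from the defining rule and not from the test.

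**Where the effect fades.** Only two of four abnormalities are needed, so a marker that is rarely abnormal contributes little to the label. With independent markers and adjacent-visit correlation 0.7, the fourth marker gave p<0.05 between groups as follows.

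| Abnormal rates of the other three | Rate of the fourth | Fourth marker p<0.05 |
|---|---|---|
| 50%, 50%, 50% | 2% | 6% |
| 50%, 50%, 50% | 10% | 24% |
| 60%, 60%, 30% | 20% | 70% |

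**The case against.** **The study is exploratory, and a formal analysis plan is promised before database lock.** That limits the severity. It does not remove the point, because the article already names the outcome, the contrast and the model, and an analysis plan that follows it inherits the problem.

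**No p value is promised in that paragraph.** This is correct. The sentence on p values and 95% CIs closes the paragraph on trial outcomes, and a reader who attaches it to the marker comparison goes beyond the text. A longitudinal model of a group difference still yields an inferential estimate, and the selection biases the estimate as well as any test.

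**The primary-objective paragraph might seem to hold a second circular test.** It says "each of the cellular markers will be assessed as a continuous outcome", just after the between-group regression. The sentence names no group contrast. What follows is "The change in cellular markers between each time point will be correlated with the number of days on antibiotics using Spearman" and one-sample t tests of change between time points, neither of which uses the label. That passage does not support the concern.

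**A reader might infer that the difference is guaranteed for each marker.** It is not, as the last table shows. The size and time course of the differences also remain useful as description.

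**The term cellular markers is broader than the four.** Immune phenotyping lists others, such as B cells, NK cells, dendritic cells and PD-L1. Striking all cellular markers from the comparison would lose valid contrasts. The PCT and CRP half of the sentence is sound too.

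**Change in all patients is already planned.** The one-sample t tests carry no restriction to the label. This stands and makes the fix easier, but the tests are listed under the primary objective, while the secondary-objective paragraph offers the conditioned contrast.

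**Conclusion.** Wrong as written, of moderate severity, and confined to the secondary-objective paragraph of the Data analysis plan. For HLA-DR, CD88, PD-1 and the regulatory T-cell percentage, a difference between suppressed and recovered states, or between the two groups, is largely produced by the definition and by regression to the mean. For commonly abnormal markers it is often or nearly always significant without true subgroups or true change, so it is not evidence of a distinct phenotype or of immune recovery. If real recovery occurs, its estimated size would be mixed with this artefact.

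The rates rest on assumed cut-offs, correlations and absence of trend. The direction held in every setting with commonly abnormal markers; the size varied, most of all for the state contrast.

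A reader might infer that the main result of the study falls too. It does not: antibiotic duration is not part of the label, so this circularity does not touch the primary comparison or its sample size.

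**What to change.** In the secondary-objective paragraph of the Data analysis plan:

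1. Limit inference on group or state differences to PCT, CRP and cellular markers outside the definition. State which markers count as defining; HLA-DR on monocyte subsets, for example, overlaps closely with monocyte HLA-DR.
2. Report the four defining marker families by group or state descriptively, alongside the PCT and CRP trajectories, without tests of difference. Say that selection by the definition and regression to the mean contribute to what is shown.
3. Answer the secondary objective with marker change over days 1–7 in all sampled patients, whatever their label. The planned tests of change between time points can be assigned to this objective.

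The cost is wording only: no new data, no change to the 180 patients and no change to the primary comparison. What is lost is a set of tests on the defining markers that would not have been interpretable.

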### Rationale

The ADAPT-Sepsis trial will include a heterogeneous population of adult patients with sepsis, including those with sepsis-induced immunosuppression. As a phenotype associated with hospital-acquired infections and reduced infection-free survival, there may be heterogeneity in the effect of the biomarker-guided antibiotic duration intervention for patients with this phenotype. If biomarker-guided antibiotics are ineffective in patients with sepsis-associated immunosuppressed, then a greater degree of patient stratification may be required to ensure optimal antibiotic duration. Furthermore, if CRP and PCT levels fall over the same period that cellular defects resolve, this may give clinicians greater confidence in following biomarker-guided antibiotic durations.

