### Sampling and data collection

As a substudy within the ADAPT-Sepsis trial, all RISC-sepsis procedures and sampling will occur within the trial. Sampling will occur during the ADAPT-Sepsis intervention period when blood is sampled daily. While additional blood samples are taken from patients for RISC-sepsis, there is no increase in number of sampling episodes. Patients will have blood sampled on alternate days up to four sampling points (days 1, 3, 5 and 7). Blood for flow cytometric analysis will be collected in Cyto-Chex (Streck, La Vista, USA) blood preservation tubes before shipping to a central testing hub (Newcastle University). Serum will be collected, frozen and stored at site until the end of the recruitment period.

Baseline clinical data and outcome data will be obtained from the ADAPT-sepsis data collection. Baseline data will include admission diagnosis, site of infection, acute physiology and chronic health evaluation (APACHE) II and sequential organ failure assessment scores and sepsis bundle care elements in the first 24 hours. In addition, at each RISC-sepsis sampling point, the circulating white cell count and differential count will be recorded.

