### Blood sample analysis

Flow cytometric analysis will be performed on a single centralised (Newcastle University) BD FACSymphony A5 flow cytometer (Becton Dickinson Biosciences, San Jose, California, USA, from here BDB). Daily internal quality control will be performed using Cytometry Setup and Tracking beads (BDB).

Leucocyte staining will be performed using antibody:fluorophore conjugates supplied by BDB. Samples will be processed according to a standard operating procedure.

At each time point, serum will be collected for measurement of PCT and CRP. These will be batched and processed by ELISA at the end of the recruitment period.

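### PCT and CRP are related to immune recovery only through a dichotomised phenotype, and the recovery contrast rests on patients seen to change state by day 7 and is mixed with time trend

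*Protocol article*

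**What the plan says.** All places are in the protocol article.

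- **Rationale:** clinicians could have more confidence in biomarker-guided durations "if CRP and PCT levels fall over the same period that cellular defects resolve".
- **Secondary objective:** to follow the leucocyte surface markers over the intervention period. PCT and CRP are not named there; the Outcomes section lists them as secondary measures.
- **Definition of sepsis-associated immunosuppression:** two or more of four abnormalities "that persist for 3 or more days". Every other patient is non-immunosuppressed, so the label belongs to the patient.
- **Sampling and data collection:** "Patients will have blood sampled on alternate days up to four sampling points (days 1, 3, 5 and 7").
- **Blood sample analysis:** "At each time point, serum will be collected for measurement of PCT and CRP".
- **Data analysis plan, secondary objective:** "we will assess the difference in the PCT/CRP levels and cellular markers for patients who met the criteria for" the phenotype "and when immune profile recovered", meaning that the patient moved to the other label. The next sentence adds: "we will compute a longitudinal analysis (taking time as a random effect) to assess the difference in the two groups".
- **Data analysis plan, continuous markers:** "The change in cellular markers between each time point will be correlated with the number of days on antibiotics using Spearman’s correlation coefficient". One-sample t tests of change between time points are also planned. Neither analysis involves PCT or CRP.

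**The concern.** The Rationale's question concerns movement within a patient: do PCT and CRP come down as the markers normalise? The design supplies matched PCT, CRP and marker values at every sample. Yet each analysis in which PCT/CRP appear replaces the markers by a two-level state or group, and each analysis that keeps the markers continuous leaves PCT/CRP out.

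Three consequences follow.

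- The contrast between meeting the criteria and recovering can be informed only by patients who are seen to do both within four samples.
- In those patients recovery comes after suppression by construction, so the contrast carries any general decline in PCT/CRP during treated sepsis.
- The longitudinal sentence could mean the two states within recovered patients, recovered against not recovered patients, or the two phenotype groups of the Definition section. These are different analyses.

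At stake is whether the study can support its suggestion that falling PCT/CRP reassures clinicians about immune recovery.

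**Working it through.** **1. Evaluable patients (the plan's own figure).** Inputs from Sample size: difference 3 days, SD 6 days, 90% power, 5% alpha, 5% withdrawal. Two-sided testing and equal groups are assumed here.

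n per group = 2(1.960 + 1.282)² × 6² / 3² = 2 × 10.51 × 4 = 84.1, so 85. The total is 170, and 170/0.95 = 178.9, so 179. This agrees with the stated 180. After 5% withdrawal, 180 × 0.95 = 171 patients remain. The calculation concerns antibiotic duration; the article gives none for the PCT/CRP analysis.

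**2. What the schedule can show.** Mark each of the four samples A (two or more abnormalities) or N (fewer), which gives 16 patterns. Read recovery as at least one N after the phenotype has been met.

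| Reading of 3 or more days | Patterns that enter | Patterns that enter and then show recovery | Samples that can show recovery |
|---|---|---|---|
| Days counted inclusively (two consecutive A) | 8 | 4: AAAN, AANA, AANN, NAAN | days 5 and 7 |
| Days elapsed (three consecutive A) | 3 | 1: AAAN | day 7 only |

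These are counts of patterns, not of patients; the patterns are not equally likely.

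**3. How many patients that could be.** The article gives neither phenotype prevalence nor recovery rate, so both are assumed. Number = 171 × prevalence × recovery by day 7:

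| Prevalence | 10% recover | 30% | 50% | 70% |
|---|---|---|---|---|
| 30% | 5 | 15 | 26 | 36 |
| 50% | 9 | 26 | 43 | 60 |
| 70% | 12 | 36 | 60 | 84 |

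The range is 5/171 = 3% to 84/171 = 49%. The changers would be a majority only if prevalence × recovery exceeded one half.

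**4. Mixing with time.** Compare the mean day of the qualifying samples with the mean day of the recovered samples:

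- AAAN: days 1, 3, 5 (mean 3) against day 7, so 4 days later.
- AANN: days 1, 3 (mean 2) against days 5, 7 (mean 6), so 4 days later.
- AANA: days 1, 3 (mean 2) against day 5, so 3 days later.
- NAAN: days 3, 5 (mean 4) against day 7, so 3 days later.

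If log PCT falls by δ per day in everyone, whatever the immune markers do, the unadjusted contrast is 3δ to 4δ with no link to immune recovery. Under the elapsed reading, recovered state and day 7 coincide in every patient who changes. Visit can then be adjusted for only by bringing in other patients.

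**5. Can a power be stated?** A paired t test (two-sided 5%, noncentral t, not adjusted for visit) across the 5 to 84 patients of step 3 gives 8% to 78% for a standardised change of 0.3, 14% to 99% for 0.5, and 28% to nearly 100% for 0.8. The answer depends wholly on inputs that the article does not give.

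**The case against.** The strongest reply has four parts.

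**The longitudinal sentence may use everyone.** The two groups of the Definition section together cover all patients, and PCT/CRP are measured at every time point. This stands in part. A reader might infer that the question is tested only in patients who enter and leave the phenotype and that most of the data are discarded. The article does not support that: the longitudinal model may include all patients, and the continuous marker analyses are not limited to those who recover. Even on the widest reading, though, that model compares dichotomised groups and does not relate PCT/CRP to the markers within a patient.

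**Tracking PCT/CRP against the markers is not the listed objective.** This is correct. It is a point of the Rationale, and the listed secondary objective concerns the markers themselves. But the Data analysis plan places the PCT/CRP comparison under that objective, so its form matters.

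**Low power is not shown.** This stands. A reader might infer that the contrast has little power and that a null result would say nothing. With 17 changers and a standardised change of 0.8, the unadjusted paired test has 87% power. A simulation that showed low power would rest on assumed prevalence, recovery, coupling and noise, and a linear coupling would favour the continuous model from the start.

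**Model form belongs in the analysis plan, and adjusting for visit removes the shared decline that the Rationale describes.** A formal plan is promised before database lock and could add the model. The article nevertheless names a specific contrast, and the point is about that choice. A decline shared by all patients can be described without a model. It does not show that the patients whose markers recover are those whose PCT/CRP fall.

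**Conclusion.** The point holds in a limited form. The article relates PCT/CRP to immune status only through a dichotomised state or group, although matched continuous values are planned at every sample.

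The recovery contrast can draw on days 5 and 7 at most, or on day 7 alone under the stricter reading of the persistence rule. It rests on a minority of patients, about 3-49% of 171, if prevalence is 30-70% and recovery 10-70%; both ranges are assumed. Its recovered samples lie 3 to 4 days after the qualifying ones on average, so without visit adjustment it cannot separate immune recovery from a general decline. The groups in the longitudinal analysis are not identified.

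No power can be derived for this analysis, and the study calls itself exploratory. This is an avoidable weakness in a secondary analysis. It does not touch the sample size or the comparison of antibiotic duration.

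**What to change.** In the formal analysis plan, before database lock:

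1. Add to the secondary-objective analysis a within-patient model in all patients. Regress log PCT and log CRP at each sample on the continuous markers from the same sample, each marker split into the patient's mean and the deviation from it. Fit visit as a fixed effect and patient as a random effect. The coefficient on the deviation answers the Rationale's question.
2. Keep the suppressed-versus-recovered contrast as a descriptive supplement, with the number of patients who contribute to it.
3. State which two groups the longitudinal analysis compares.

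The cost is some wording and one extra model for each biomarker; no new samples are needed. The downside is that the result becomes a slope, which is less immediate to readers than a difference between two states.

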### Sample size

The sample size is based on detection of a difference in antibiotic durations between the ‘sepsis-associated immunosuppression’ and ‘non-immunosuppressed’ groups. The 2016 Surviving Sepsis Campaign guidelines recommended 7–10 days of antibiotics for patients with sepsis.^27^ We have assumed that patients with sepsis-associated immunosuppression will have longer durations (10 days) and so with a SD of 6 days (derived from the ADAPT-sepsis trial), then a sample of 180 patients is required to detect a difference of 3 days in antibiotic treatment between the ‘sepsis-associated immunosuppressed’ and ‘non-immunosuppressed’ patients with 90% power, a 5% alpha and a 5% withdrawal rate.

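### The secondary longitudinal model names time as its only random effect; the patient, who is the clustering unit, should be named and time should have a fixed effect

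*Protocol article*

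**What the plan says.** The Secondary objective section of the protocol article sets the aim: "To monitor changes in expression of leucocyte surface markers (primary outcome measures) over the time course of the ADAPT-Sepsis biomarker-guided antibiotic duration intervention period". Under Sampling and data collection, the schedule is fixed in advance: "Patients will have blood sampled on alternate days up to four sampling points (days 1, 3, 5 and 7".

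For this objective, the Data analysis plan compares PCT, CRP and the cellular markers between patients who met the immunosuppression criteria "and when immune profile recovered (ie, became ‘non-immunosuppressed". The model is given in one clause: "we will compute a longitudinal analysis (taking time as a random effect) to assess the difference in the two groups". Nothing else about its structure is stated. In particular, no patient effect, within-patient covariance or fixed time term appears.

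The paragraph on the primary objective adds a separate analysis of change: "One sample t tests will be used to assess the changes between time points". The section opens with a promise of further detail: "A formal analysis plan will be finalised and deposited on an open access platform before the database is locked".

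**The concern.** A random effect suits units that are a sample from a larger population and that induce correlation among their own observations. Here that unit is the patient. Sampling days 1, 3, 5 and 7 are four levels chosen by design, and change across them is what the secondary objective is about, so time belongs in the fixed part of the model.

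A random effect for sampling day alone says that samples taken on the same day share something and that, given the day, two samples from one patient are as unrelated as two samples from different patients. Serial samples from a critically ill patient over a week are unlikely to behave that way. If the clause is carried into the analysis as it stands, the standard errors, confidence intervals and p values for the comparison between groups will be wrong. The direction of the error depends on a second matter that the text leaves open: whether group is a fixed label for each patient or a state that a patient can leave.

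**Working it through.** **The plan's own figures.** The document gives no figure for the longitudinal model, so there is none to reproduce. The stated sample size of 180 does reproduce: a difference of 3 days, "with a SD of 6 days (derived from the ADAPT-sepsis trial"), 90% power and 5% alpha (two-sided and 1:1 assumed) give 2 × (1.960 + 1.282)² × 6² / 3² ≈ 84.1, so 85 per group; 85 / 0.95 = 89.5, so 90 per group and 180 in total. That figure concerns antibiotic days and has no bearing on this point. It is used only to set the number of patients in the simulations: 180 × 0.95 = 171.

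**Inputs.** Samples per patient: m = 4, the maximum under Sampling and data collection. Within-patient correlation (ICC): not given in the document, so 0.3, 0.5 and 0.7 are assumed.

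**Reading 1: group fixed per patient, random effect for day only.** The true variance of the group difference exceeds the model's by the design effect DE = 1 + (m − 1) × ICC. The standard error is understated by √DE, and the true type I error of a nominal two-sided 5% test is 2 × [1 − Φ(1.96 / √DE)].

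| ICC | DE | √DE | Type I error, formula | Type I error, simulated | Simulated, patient as unit |
|---|---|---|---|---|---|
| 0.3 | 1 + 3 × 0.3 = 1.9 | 1.38 | 15.5% | 15.9% | 5.3% |
| 0.5 | 1 + 3 × 0.5 = 2.5 | 1.58 | 21.5% | 21.8% | 4.2% |
| 0.7 | 1 + 3 × 0.7 = 3.1 | 1.76 | 26.6% | 27.3% | 4.8% |

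The simulations used 171 patients, four samples each, equal correlation between all pairs of samples and 2,000 runs per ICC. Day was handled by removing the day means. Taking the patient as the unit is equivalent to a patient random intercept in balanced data.

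**Reading 2: status changes within a patient.** The comparison is then partly within patients, and a model without the patient leaves between-patient variation in the residual. With one sample in each state, the standard error is overstated by 1 / √(1 − ICC): 1.20, 1.41 and 1.83 for ICC 0.3, 0.5 and 0.7.

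Simulations of the type I error with the patient ignored, again with 171 patients and four samples, gave the following (day is fixed or omitted here, as an approximation to the random-day model):

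| Pattern of recovery | ICC 0.3 | ICC 0.5 | ICC 0.7 |
|---|---|---|---|
| All recover mid-course, no day term | 1.9% | 0.7% | 0.1% |
| Recovery at a random visit, no day term | 4.2% | 3.3% | 2.9% |
| Recovery at a random visit, day adjusted | 6.5% | 7.9% | 8.4% |

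The exact values depend on when patients recover. The pattern is that the test is conservative in some settings and mildly anti-conservative in others, and well below the Reading 1 figures.

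**Which reading does the text support?** The section Definition of sepsis-associated immunosuppression sorts patients into two groups, and those not meeting the criteria form the second. The Data analysis plan, for the secondary objective, uses the non-immunosuppressed label for the point at which a patient recovers. The two are not reconciled, so both readings remain open.

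**Reading 3: a patient-level random slope on time.** This would largely account for the within-patient correlation, and the error rates above would not apply. Without a fixed time term, however, a random slope has mean zero, so the model would assume no average change, although average change is what the objective asks about.

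**The case against.** The strongest reply is that a condensed article leaves model structure to the formal analysis plan, and one is promised before database lock. That covers what the article does not say, such as a group-by-day term or the covariance structure. It does not cover what it does say: it states which effect is random, and an analysis plan that follows it carries the problem forward.

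A second reply is that the clause is shorthand for a random slope on time within patient. This is plausible and cannot be excluded. It is a reason to word the point as a correction to the sentence, not as proof that samples will be analysed as independent.

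A third reply is that a false-positive rate means little for HLA-DR, CD88, PD-1 and regulatory T cells, because the groups are defined by those markers and differ by construction. This stands. The error rates under Reading 1 bear mainly on PCT and CRP.

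Two stronger inferences are tempting and should not be drawn. A reader might infer that the group-by-time contrast is never estimated; the text neither specifies nor excludes such a term. A reader might also infer that the stated objective goes unestimated. The objective as worded concerns change over time and does not mention groups, and the one-sample t tests do estimate change between time points, with each patient's two samples properly paired.

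**Conclusion.** The point holds as a defect in a stated model. Time is the only random effect named, the patient is not mentioned, and followed literally the analysis gives wrong standard errors.

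The size depends on assumptions the document does not settle. With group fixed per patient, four samples each and an ICC of 0.3 to 0.7, the nominal 5% group test has a true error of about 15% to 27%. If status is time-varying, the error can run the other way, so it would be wrong to conclude that standard errors are too small in general. If a patient-level random slope was intended, the clustering is largely handled and what remains is the missing fixed time term.

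The sentence needs rewriting on every reading. This is a secondary analysis in a study labelled exploratory and leaves the primary comparison of antibiotic days untouched, so it is a change that should be made rather than a barrier to the study.

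**What to change.** Replace the parenthesis on time as a random effect with wording such as: a linear mixed model for each marker, with fixed effects for group, sampling day (categorical) and group-by-day, and a patient random intercept (with or without a patient-level random slope for time) or a within-patient covariance structure.

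Add one statement on whether group status is fixed per patient or varies over time. If it varies, enter it as a time-dependent covariate and say whether the within-patient contrast between the immunosuppressed and recovered states is the target. If a random slope was what the authors meant, say so and keep the fixed time term.

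Optionally, contrasts from this model could take the place of the one-sample t tests, so that patients with incomplete series also contribute; the t tests are not wrong in themselves.

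The cost is a sentence or two in the formal analysis plan before database lock. No extra samples, patients or data are needed.
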